### Ethical consideration

The study protocol has been approved by the University of Hong Kong and Hong Kong West Cluster Ethics Committee (UW 12–220).

## Discussion

Previously little work has been done to evaluate the effectiveness of resilience training with a marginalised group of women internationally and in particular in the Asian region his paper describes the background and methods of a randomised controlled trial of PREP, a resilience-promoting programme, which will provide evidence for this psychological intervention for improving psychological well-being and ultimately HIV prevention. Under the framework of resilience, the intervention that focuses on individual strengths can potentially expand the understanding and its application to health promotion research by integrating the missing link between psychological and behavioural risk factors.

Current HIV prevention strategies for FSWs focus on harm reduction, biomedical and structural interventions which have operated at individual and population levels. Locally, a series of studies conducted came to a similar conclusion that HIV prevention would not be effective if boarder issues such as psychological or contextual ones were not addressed [16,58]. For example, one of our studies found vaginal douching which carried an increased infection risk, remained a common practice amongst FSWs because it helped to suppress their negative feelings of “being dirty” [59], despite extensive formal education and training to the contrary. It has become apparent to the investigative team that interventions that target fundamental issues of inequity and empower FSWs in resilience strategies are the *only* effective means at reducing the prevalence of HIV/ STIs [58]. As a contribution to scholarly knowledge, this study will contribute to the understanding of resilience among these women. Furthermore, the proposed study will enable us to evaluate the impact of the intended resilience programme on each resilience attribute, namely self-esteem, self-efficacy, and coping as mechanisms of change and whether the model of resilience could improve psychological well-being and its relation to sexual health practices among FSWs in Hong Kong.

At the individual level, a new prevention programme that addresses the psychological strength of FSWs is likely to improve psychological and physical well-being. At the societal level, it is believed FSWs with a more enhanced self-esteem may be more willing to take good care of themselves and engage in a variety of sexual health-promoting behaviours (e.g. consistent condom use), which in turn can reduce the number of HIV infection and transmission of such to their clients or partners in the general population. If successful, this study can set the foundation for future guidelines for health professionals and policymakers when considering HIV prevention strategies for other at-risk populations and managing the health needs of this sub-population and possibly other at-risk population. Further cost-effectiveness evaluation of this intervention can be conducted when the current programme is shown to be effective in improving participants’ psychological outcomes and promoting sexual health behaviors. Such a programme can be disseminated to other researchers and healthcare providers at local and international conferences as well as public education programme to improve the services provided for high-risk women.

### Limitations

Participants who volunteer for the study are arguably biased towards being more motivated and health-conscious but the design of randomised control trial equalises this effect in both groups. Furthermore there is the potential for the participants to have psychological distress and therefore screening by a clinical psychologist will help exclude those who are clinically depressed and need intensive treatment. Although the outreach staff will contact the FSW recruited regularly, the attrition rate of those who are motivated but assigned to the usual care group may be diminished and hence a potential tendency to drop out from the study. The aims and objectives of the study will be clearly explained to the potential participants and the “buy-in” will be sought before they agree to participate. Given Hong Kong is effectively one large metropolis and there are considerable overlaps between the two targeted NGOs, therefore, cluster randomised control trial will not be feasible. Even though the participants recruited from the two NGOs would be told specifically not to disclose, there may still be a risk of contamination between the intervention and control group given the participants may know each other.

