#### Research aims and objectives

The Personal Resilience and Enrichment Programme (PREP) has been developed according to resilience framework for a trial with FSWs in Hong Kong. The aim of this study is to seek a new direction for HIV prevention by investigating the effectiveness of PREP in FSWs. Through promoting FSW psychological health, it is hypothesised FSWs will take better care of their physical well-being and actively practise HIV preventive measures, and hence reduce their HIV risks. Specifically, the objectives of this study include:

1. To evaluate the effectiveness of PREP, the resilience-promoting intervention, in enhancing FSWs’ overall resilience, reducing their psychological distress, and eventually reducing HIV risk behaviours among FSWs in Hong Kong.

2. To explore the mechanism of how individual resilience factors operate to promote better psychological outcomes and decreasing HIV infection among FSWs.

This study is a randomised controlled trial to test the hypothesis that the participants in intervention group, as compared to those in the control group receiving usual care, would have an improvement in HIV preventive behaviour through the increase in overall resilience and in terms of their self-efficacy, self-esteem and coping strategies. At the same time, it is hypothesised that this cohort of FSWs’ psychological distress would be reduced upon completion of the programme and such improvements would be continued at least in the 3-month post-intervention period. The study will further explore the operation of the resilience model by specifying the association of stress perceived by FSWs, and the effects of the resilience attributes (self-esteem, self-efficacy, and coping strategies) on their level of psychological health and HIV preventive behaviours (Figure 1).

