### Participants

FSWs who fulfil the inclusion criteria will be invited and have the study explained to them by the trained outreach staff of the NGOs. Inclusion criteria for the proposed study are: (i) 18 years or older; (ii) acknowledged to have been living and working as a FSW in Hong Kong within the preceding 6 months; and (iii) able to give an informed consent. All potential participants will be screened over the telephone by one of the researchers who is a clinical psychologist to confirm their fulfilment of inclusion criteria and exclude them if they are (i) unable to speak Cantonese/ Putonghua; and (ii) diagnosed with and currently on medical or psychological treatment for a serious psychological health problems such as psychosis, current substance abuse, bipolar disorder, severe affective disorders or have suicidal ideation.

Eligible participants will be provided with further details of the study and those who provide verbal consent will complete the self-reported baseline questionnaire face-to-face. Participants will be randomly allocated on a 1:1 ratio into one of the two groups according to a block randomisation list which was computer-generated. Participants are informed that they would have an equal chance of allocating into any of the two groups and the allocation outcome is unknown to participants until baseline assessment session. The women recruited will be advised not to disclose the content and activities of the intervention to others to avoid contamination. An independent researcher will conduct the baseline, post-intervention, and follow-up assessments and enter the data obtained from the questionnaires.

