### Sample size

Sample size estimation is based on the “always” use condom rate during commercial transactions in the last month at 49.3% from the latest local study published on the topic [16] and an assumption of effect size of 25% on condom use rate between the intervention and control groups from a previous study [43]. In order to detect such a difference with a power of 80% and a two-tailed significance of 0.05, the sample size required is 66 in each group.

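### About half the women are expected to be at the ceiling of the primary outcome at entry; stratify allocation and analysis by baseline condom use and state the limited headroom

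*Protocol article*

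**What the plan says.** - **Aim.** Research aims and objectives states the hypothesis as a gain: the intervention group "would have an improvement in HIV preventive behaviour through the increase in overall resilience".
- **Outcome.** The primary outcome section uses self-reported condom use with clients: always in the previous month, and at the last encounter. Both act as proxies for safe sex.
- **Expected level and target.** The Sample size section starts from the always "use condom rate during commercial transactions in the last month at 49.3% from the latest local study published on the topic", adds "an assumption of effect size of 25% on condom use rate between the intervention and control groups", and concludes that, "with a power of 80% and a two-tailed significance of 0.05, the sample size required is 66 in each group".
- **Eligibility.** Women must be adults, able to consent, and "acknowledged to have been living and working as a FSW in Hong Kong within the preceding 6 months". The exclusions concern language and serious psychological problems. No criterion concerns condom use.
- **Allocation.** "Participants will be randomly allocated on a 1:1 ratio into one of the two groups", from a computer-generated block list. The text places the baseline questionnaire before this step. No stratification factor is mentioned.
- **Analysis.** Data analyses compares change over time between groups by analysis of variance, under intention to treat.
- **Volunteer selection.** Limitations describes volunteers as "arguably biased towards being more motivated and health-conscious but the design of randomised control trial equalises this effect in both groups".

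**The concern.** On a yes/no outcome, a woman who already always uses condoms has no higher category to move to. She can stay or lapse. With 49.3% expected in that position and none screened out, any gain from conversion must come from roughly half the sample. The protocol's remark about health-conscious volunteers suggests that the share at the ceiling may exceed the 49.3% taken from another study. The only answer given is that randomisation equalises the effect between arms. Balance and headroom are different things, and randomisation supplies only the first.

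Two things are at stake. If the starting level is higher than planned, power falls, and a null result would be hard to read: the programme may not have worked, or few women may have had room to change. Separately, baseline status is likely to be the strongest predictor of follow-up status. The arms can differ on it by chance, and an analysis of raw change does not use it efficiently.

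**Working it through.** **1. The plan's own figure.** Inputs from Sample size: 49.3%, a difference of 25 points (so 74.3%), 80% power, two-sided 0.05. The two-proportion formula with continuity correction gives 66 per arm, an exact match (59 without the correction). A relative 25% (61.6%) would need 271 with the correction, so the absolute reading is the one used. Power at 66 per arm without the correction is 85%.

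**2. Women with room to improve.** At the ceiling: 0.493 × 132 = 65.1. Able to improve: 0.507 × 132 = 66.9, or about 33.5 per arm.

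**3. What 25 points implies.** If always-users contribute nothing to the difference, the required difference in conversion is 0.25 / 0.507 = 49% of the non-always-users. If instead 15% of always-users lapse under usual care and PREP prevents every lapse (assumed), that supplies 0.493 × 0.15 = 7.4 points, leaving (0.25 − 0.074) / 0.507 = 35%. The implied range is therefore about 35% to 49%. The protocol does not discuss it.

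**4. A higher starting level.** The documents give no rate for volunteers, so these baselines are assumptions. Holding conversion at 49% and using 66 per arm (no continuity correction):

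| Baseline always-use | Follow-up with PREP | Power |
|---|---|---|
| 49.3% | 74.3% | 85% |
| 55% | 77.2% | 77% |
| 60% | 79.7% | 70% |
| 70% | 84.8% | 53% |

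**5. Chance imbalance at baseline.** SD of the between-arm difference = √(2 × 0.493 × 0.507 / 66) = 0.087, or 8.7 points. Simple blocking on arm size does not reduce this.

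**6. What using the baseline stratum gains.** Illustrative assumptions: baseline 49.3%, 66 per arm, no dropout. In the base case, usual care keeps 85% of always-users and converts 15% of the others; PREP converts 45%. Retention under PREP is then varied, as are the usual-care rates. Power is by simulation. The change-score column is a two-group test on follow-up minus baseline, equivalent to a group-by-time ANOVA with two time points. The stratified column is a Mantel–Haenszel test on all women. The last column is an unadjusted test in baseline non-always-users only. Figures move by about a point with the exact test used.

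| Retention, usual care → PREP | Conversion, usual care → PREP | Change score, all | Stratified, all | Non-always-users only |
|---|---|---|---|---|
| 85% → 85% | 15% → 45% | 46% | 57% | 78% |
| 80% → 80% | 20% → 45% | 30% | 39% | 60% |
| 90% → 90% | 10% → 45% | 69% | 78% | 92% |
| 85% → 95% | 15% → 45% | 78% | 86% | 78% |
| 80% → 90% | 20% → 45% | 57% | 68% | 60% |

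The stratified whole-sample analysis beats the change score in every row. The subgroup is best only when PREP does nothing for always-users (first three rows), and loses to the stratified analysis when PREP also prevents lapses (last two).

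**The case against.** Much of the opposing case stands.

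- **A reader might infer that the Limitations section claims randomisation removes the ceiling.** It does not. It says only that volunteer motivation is equalised between groups, which is correct in expectation, and it never mentions a ceiling. The sentence is incomplete rather than false.
- **A reader might infer that the sample size is wrong.** It is not. The 49.3% is an input, so always-users are already counted in the 66 per arm, and the figure reproduces exactly. Whether 25 points is attainable rests on a cited study that is not available here.
- **A reader might infer that always-users carry no information, so the trial should enrol or chiefly analyse inconsistent users.** That holds only if PREP cannot prevent lapses. The protocol hypothesises improvements lasting at least three months and speaks of consistent condom use, so maintenance is a plausible route of effect. The programme is meant for sex workers generally, and the all-comer comparison is a legitimate target that intention to treat addresses.
- **Stratification factors and subgroup readings are often left to a fuller document.** Agreed, and their absence is not counted as an error. What this article does state is an unqualified block list, an analysis of variance on change, and an answer to volunteer selection that stops at balance. If a fuller document already stratifies and adjusts, most of the fix is in place.

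None of this creates headroom or makes a raw change analysis efficient for this outcome.

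**Conclusion.** This is a weakness of design and efficiency, not an arithmetic error, a contradiction or an invalid comparison. On the plan's own 49.3%, about 65 of 132 women cannot improve on the previous-month outcome, and the share among health-conscious volunteers is probably larger. Last-encounter use has a ceiling too, but no expected rate is given for it.

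If volunteers start at 60% to 70% and conversion stays at 49%, power falls from 85% to between 70% and 53%. Those baselines are assumptions. The chance imbalance of 8.7 points (SD) follows directly from the plan's figures. The gain from stratifying and adjusting is about 8 to 11 points of power across the scenarios tried; its direction was the same in all of them, while its size depends on the assumed retention and conversion rates. Stratification does not restore headroom. It makes better use of the headroom there is and, with the secondary results below, makes a null result easier to interpret.

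**What to change.** 1. **Allocation.** Stratify the block list by baseline condom use with clients (always / not always in the previous month). This needs the questionnaire completed before the allocation is drawn, which is the order the Participants section describes.
2. **Primary analysis.** Keep the whole-sample intention-to-treat comparison, but stratify or adjust it for that baseline status in place of a plain change-score ANOVA.
3. **Secondary results.** Prespecify conversion among baseline non-always-users and maintenance among always-users, each by arm, reported beside the pooled result.
4. **Limitations text.** Keep the statement on balance between arms, and add that motivated volunteers may leave less room for improvement on the primary outcome.

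Do not restrict entry to inconsistent users, and do not make that subgroup the main reading.

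The cost is two block lists instead of one, a different model for one outcome, and a few lines of text. The baseline item is already collected. If recruitment has started, items 2 to 4 can still be adopted before the outcome data are examined by arm.

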## Abbreviations

AFRO: Action for REACH OUT; FSWs: Female sex workers; NGOs: Non-governmental organisations; PREP: Personal resilience and enrichment programme; STIs: Sexually transmitted infections; SEM: Structural equation modelling; WHO: World health organization.
